### Data analysis

Descriptive statistics will be used to describe the baseline characteristics in the historical control and active group. Primary end points will be calculated, and a chi square test will be used to assess if the difference between pre and post-test is significant for the primary outcomes (nominal data), with *p* < 0.05 considered significant.

Univariate analysis will be undertaken for each of the outcomes to compare differences in the characteristics of the historical control versus the three year active intervention. For continuous variables, the data will be tested for normality using Shapiro Wilk test and equality of variances using Levene’s test. If these assumptions hold true, parametric tests like the t-test or ANOVA will be used. If these assumptions do not hold then nonparametric alternatives will be considered. For categorical variables a Chi Squared test will be used. When comparing multiple groups, post hoc investigations may be included with Bonferroni corrections. Regression models will be used to control for co-variates.

The analysis will be undertaken 3 years prior to study commencement (historical control) and then interim analysis yearly until trial conclusion.

Survey responses will be analysed to understand the usability of FHT software and if practice staff felt the software aided their management of CKD. Semi structured interviews of practice champions and additional primary care physicians will be conducted via zoom or phone, according to interviewees preference. Interview transcripts will be coded by at least two researchers. The clinical performance feedback intervention theory framework will be used for the overall implementation evaluation combining survey and interview data [12].

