## Methods

### Study design

This will be a pragmatic implementation trial using an interruptive time series design comparing outcomes in the three years prior to trial commencement with three years of active trial. Primary care data will be linked with tertiary care administrative data to enable analysis of broader health service impact. The overall program evaluation will use a mixed methods approach using the clinical performance feedback intervention theory framework [12].

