Earlier detection and management of CKD requires time for improvements to be realised, hence a three-year trial duration was chosen. One limitation of a pre-post implementation trial with a historical control is the inability to assess direct causation. This approach was chosen given the practical challenges of a randomised trial in primary care over three years in addition to the ethical challenges of preventing practices from undertaking quality improvement and CKD educational activities over this extended duration. To help address this limitation an interrupted time series design has been chosen with a 3-year retrospective control compared to the 3-year prospective intervention used to assess the rate of change in parameters over time. This will assist in determining if improvements are due to a natural increase in screening, diagnosis, and management over the course of time, or associated with the intervention.

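### The only test named for the primary outcomes is a pre-versus-post chi-square with no time term, so it cannot do what the interrupted time series design is relied on to do

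*Protocol article*

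**What the plan says.** The Abstract, Study design and Discussion all describe an interrupted time series. Study design calls it an "interruptive time series design comparing outcomes in the three years prior to trial commencement with three years of active trial". The Discussion accepts that a historical control cannot show direct causation and offers the time series as partial remedy, with the "3-year prospective intervention used to assess the rate of change in parameters over time". It adds: "This will assist in determining if improvements are due to a natural increase in screening, diagnosis, and management over the course of time", as opposed to being associated with the intervention.

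The Data analysis section says of the primary endpoints that "a chi square test will be used to assess if the difference between pre and post-test is significant for the primary outcomes (nominal data"). The threshold is a p-value below 0.05. It then describes univariate work to "compare differences in the characteristics of the historical control versus the three year active intervention", using t-tests, ANOVA, nonparametric alternatives or chi-square, and ends the paragraph with "Regression models will be used to control for co-variates". It names no time variable, pre-intervention slope, level change or slope change.

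Under Outcomes, the primary outcome is the change in the number of patients meeting indicators for screening, diagnosis and management of chronic kidney disease (CKD).

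**The concern.** The design and the stated analysis do not match. An interrupted time series can offer some protection against background change because the pre-intervention trend is projected forward and the post-intervention data are judged against that projection. A two-period chi-square sees only how many patients met the indicator in each period and how many did not. The order and timing of events within each period are lost.

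This matters because the article describes no concurrent control, which leaves the pre-intervention trend as the main safeguard. The Discussion itself treats a natural increase as possible. One indicator is a running total of coded CKD diagnoses, a chronic label that could accumulate in records without any intervention. As written, a significant primary result could not be told apart from a continuing trend.

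**Working it through.** **Nothing to reproduce.** The article states no sample size, power or effect size. The figures below illustrate how the named test behaves when FHT has no effect. They do not estimate the bias in this trial.

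**Inputs from the article:** chi-square, pre versus post; threshold 0.05; 3 years before and 3 years after.

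**Assumptions not in the article:** each 3-year window is pooled; the background trend is linear at *t* percentage points per year through both windows; patients are independent; baseline proportion and patients per period (*N*) as given below.

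**Step 1: the spurious difference.** The window midpoints lie 1.5 years before and 1.5 years after the start, so they are 3 years apart. With no FHT effect the two means differ by 3 × *t*.

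**Step 2: the rejection probability.** Null SE = √(2·p̄(1−p̄)/N); z = difference / SE; probability of rejection ≈ Φ(z − 1.96), the other tail being negligible in these examples. Take a pre-period mean of 30%.

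- *t* = 0.5, *N* = 10,000: difference 1.5 points; p̄ = 0.3075; SE = √(2 × 0.3075 × 0.6925 / 10,000) = 0.00653; z = 0.015/0.00653 = 2.30; Φ(0.34) ≈ **63%**.
- *t* = 1, *N* = 10,000: difference 3 points; p̄ = 0.315; SE = √(2 × 0.315 × 0.685 / 10,000) = 0.00657; z = 0.03/0.00657 = 4.57; Φ(2.61) ≈ **99.5%**.

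**Step 3: sensitivity to the assumptions.** Rejection probability with no FHT effect, both tails included, where the baseline is now the proportion at the start of the intervention:

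| Baseline | Trend (points/year) | N = 1,000 | N = 5,000 | N = 15,000 | N = 50,000 |
|---|---|---|---|---|---|
| 20% | 0.1 | 5% | 7% | 10% | 22% |
| 20% | 0.5 | 13% | 47% | 90% | 100% |
| 20% | 1 | 39% | 96% | 100% | 100% |
| 50% | 0.1 | 5% | 6% | 8% | 16% |
| 50% | 0.5 | 10% | 32% | 74% | 99.7% |
| 50% | 1 | 27% | 85% | 99.9% | 100% |

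The problem therefore depends on trend and denominator together. At 0.1 points per year and 1,000 patients the rate stays near the nominal 5%.

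**Step 4: does a trend-adjusted model repair it?** A simulation (24 quarters, 4,000 replicates, 50% baseline, 5,000 or 15,000 per period, trends of 0, 0.5, 1, 2 and −1 points per year, no FHT effect) applied both methods to the same data. A joint test of level and slope change in a segmented regression rejected in 4.7% to 5.8% of replicates throughout. The chi-square rejected in about 5% at zero trend, 32% to 75% at 0.5 points per year and 85% to 100% at 1 point per year. The simulated data were linear and had no autocorrelation or clustering, so they favour the segmented model.

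**Step 5: the opposite error.** A true step of +3 points on a trend of −1 point per year leaves the window means equal: 3 + 3 × (−1) = 0. With 15,000 per period the chi-square rejected in 4.4% of simulations and the segmented regression in 63.6%.

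**The case against.** The strongest defence is that a journal article condenses, and that the segmented-regression detail may sit in a full protocol or SAP that is not shown. The Discussion does state the intent to assess rates of change, and the unspecified regression models could include time. This stands against one stronger reading that a reader might infer, namely that the time series will never be analysed: the article does not support that. It does not remove the contradiction. The Data analysis section is not silent; it commits to a particular test and threshold for the primary outcomes, and the regression sentence is not tied to that decision.

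A second stronger reading is that any background trend will be counted as success. That also fails. Only a favourable trend that is large for its denominator would do so, and the Discussion disclaims direct causation and speaks only of association.

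A reader might also apply the calculation to the whole estimated population of 150,000. That fits none of the indicators at a 30% baseline. Screening is limited to at-risk patients, and management to CKD patients with at least 12 months of follow-up. Only coded diagnosis could use everyone, and there 30% does not sit with the Background's global figure of just over 10% or with the under-coding acknowledged under Outcomes.

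Two further cautions stand. Pooling of each window is the natural reading but not the article's word; a comparison of two time points would ignore trend equally, with a different multiplier from 3. Independence is doubtful, because largely the same patients in 20 practices probably contribute to both periods. The direction of that error has not been worked out.

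**Conclusion.** The point holds as a contradiction within the article: the test fixed for the primary outcomes cannot support the inference for which the design was chosen, and no time-based model is specified for those outcomes. The qualitative conclusion rests on the article alone, since a two-period chi-square has no time term whatever the data. The size rests on assumptions about trend, baseline, denominator, linearity and independence, none of which the article supplies. Over the values tried, false rejection runs from the nominal 5% to near certainty. The claim is about what the named test can show. It does not say that a trend exists in these practices or that FHT has no effect.

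**What to change.** In the Data analysis section, replace the chi-square as primary analysis with a segmented regression of each indicator's proportion over regular intervals (for example monthly or quarterly) across the planned 3 years before and 3 years after. Include pre-trend, level-change and slope-change terms, and allow for autocorrelation and for clustering by practice. Report the difference between the fitted post-intervention value and the extrapolated pre-trend with a 95% confidence interval. Keep the chi-square, or the raw pre and post proportions, as description only.

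The management indicator needs its own definition of the series. It requires at least 12 months of follow-up after a CKD diagnosis, so patients diagnosed after the start cannot qualify in the first year, and some follow-up windows cross the start. The series should be defined so that this is accounted for.

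The cost is protocol wording and programming, on data that the Data collection and management section already plans to extract. The downside is a wider confidence interval than the simple pre/post contrast gives.

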**Methods:**

This pre-post implementation trial using an interrupted time series design will evaluate the clinical and service outcomes of Future Health Today, using a mixed methods study in twenty general practices with an estimated population size of 150,000. Deidentified patient data will be extracted from participating practices to examine the primary aims of the study. Surveys and semi-structured interviews with general practice will inform secondary hypotheses. Data linkage between primary care and tertiary care data will examine the broader health service impacts.

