#### Recruitment

 Recruitment will take place at the practice level and will focus on practices who have been identified to serve a patient population with a significant burden of chronic disease with complex care needs. These practices have been identified through a hospital program to support patients with high risk of hospital re-admission in the context of chronic disease. Recruitment will then be expanded to the broader tertiary centre catchment area as required.

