### Data collection and management

Three years of historical primary practice data will be collected (historical control) and compared with three years of active intervention. Primary practice data will be extracted from the primary care electronic medical record and FHT database in a non-re-identifiable format using software Grhanite™ [14]. Grhanite™ software enables data linkage without needing re-identification of patient data [14]. FHT usage will be extracted from the FHT monitoring system. Hospital utilisation, including admission and outpatient attendance to relevant specialties will be extracted from the hospital electronic record system. Hospital data will be converted to a non-re-identifiable format using Grhanite™ prior to being provided to the research team and then subsequently linked to the primary care data. All data will be housed on a secure server. Survey data will be collected using REDCap electronic survey and data capture tools hosted by Western Health [15, 16]. REDCap is a secure web-based software platform designed to support data capture for research studies [15, 16]. Practice interviews will be recorded and transcribed using a voice-to-text function, and then manually checked for accuracy.

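### The primary pre/post chi-square assumes independent records, but the data come from the same 20 practices in both periods, so p < 0.05 is not a 5% error rate

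*Protocol article*

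**What the plan says.** In the Protocol article, Data analysis, the significance test for the three primary domains (screening, diagnosis, management) is fixed: a "chi square test will be used to assess if the difference between pre and post-test is significant", "with *p* < 0.05 considered significant". The only further modelling named there is regression to adjust for covariates. No section names a paired, clustered, mixed, GEE or robust-variance method.

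The data structure is set out elsewhere:

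- Abstract, Methods: the study covers "twenty general practices with an estimated population size of 150,000", and "Deidentified patient data will be extracted from participating practices to examine the primary aims of the study".
- Recruitment: "Recruitment will take place at the practice level". Under Intervention, the software, training, education session and practice champion are all supplied to practices.
- Data collection and management: "Three years of historical primary practice data will be collected (historical control) and compared with three years of active intervention".
- Outcomes: the primary outcome counts patients who meet an indicator. Secondary outcome 1.7 foresees subgroups by intensity of software use if practices turn out to differ.
- Study design and Discussion: the design is declared to be an interrupted time series that looks at rates of change.

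**The concern.** An ordinary chi-square compares two sets of independent patients. This design departs from that in two ways, which act in opposite directions.

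1. **Practice.** The programme acts through practices, so the change in an indicator will differ from one practice to another. Outcome 1.7 anticipates uneven uptake. This variation does not cancel in a pre/post difference, and having many patients per practice does not average it away. There are only 20 practices to average over.
2. **Patient.** The same practices supply both periods, so many patients are likely to be counted in each. Positive correlation within patients makes the true standard error of the difference smaller than the chi-square assumes.

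At stake is the decision rule for all three primary domains. In a large domain, chance drift in a few practices could be declared a programme effect. In a small one, a real effect could be missed.

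**Working it through.** **The plan's own figure.** The article states no sample size, power or effect size, so there is nothing to reproduce. As a baseline, with fully independent records the chi-square has a type I error of 5.0%.

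**Inputs from the article.** 20 practices; about 150,000 people, hence 150,000 / 20 = 7,500 per practice on average; significance at 0.05 (a chi-square is two-sided).

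**Assumed inputs (the article gives none).** Baseline proportion 30%; N patients seen in both periods; within-patient correlation ρ = 0.6; equal practice sizes; zero average change; between-practice SD of true change 1, 2, 3 or 5 percentage points; N = 5,000, 15,000, 40,000 or 150,000. For scale, 15,000 is 10% of 150,000, 10% being the round figure in Background for world prevalence of CKD.

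**Formulas.**

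- SE implied by the chi-square: s₀ = √(2 × 0.3 × 0.7 / N)
- True SE: s₁ = √(s₀² × (1 − ρ) + SD² / 20)
- Actual type I error: 2 × (1 − Φ(1.96 × s₀ / s₁))

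**Worked example, N = 40,000, SD 3 points.** s₀ = √(0.42 / 40,000) = 0.324 points. s₁ = √(0.324² × 0.4 + 3² / 20) = 0.701 points. The ratio is 2.16 and the type I error 36.5%.

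**Results: actual type I error at nominal 5%.**

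| N | s₀ (points) | SD 1 | SD 2 | SD 3 | SD 5 |
|---|---|---|---|---|---|
| 5,000 | 0.917 | 0.4% | 1.4% | 4.3% | 15.4% |
| 15,000 | 0.529 | 1.0% | 6.3% | 16.7% | 37.4% |
| 40,000 | 0.324 | 3.6% | 19.7% | 36.5% | 57.6% |
| 150,000 | 0.167 | 18.5% | 47.5% | 62.9% | 77.0% |

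At 150,000 and SD 3 points, s₁ = 0.679 against s₀ = 0.167, a ratio of 4.1.

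**Where the direction turns.** The two effects balance when SD = s₀ × √(20 × 0.6) = 3.46 × s₀. That is 3.2, 1.8, 1.1 and 0.6 points for the four values of N. Below that spread the test is conservative; above it, anti-conservative.

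**Second parameterisation.** Let m be the eligible patients per practice, ICC the intra-practice correlation, CAC the correlation of a practice's effect between periods, and τ the within-patient correlation. The true variance divided by the chi-square variance is DE = 1 + (m − 1) × ICC × (1 − CAC) − overlap × τ, and the type I error is 2 × (1 − Φ(1.96 / √DE)).

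- Stable practice effects only (CAC = 1, no overlap): DE = 1.0, type I error 5.0%.
- Repeated patients only: 50% overlap with τ = 0.3 gives DE = 0.85 and 3.4%; 90% with τ = 0.7 gives DE = 0.37 and 0.1%.
- Both, overlap × τ = 0.4: m = 750, ICC 0.01, CAC 0.95 gives DE = 1 + 749 × 0.01 × 0.05 − 0.4 = 0.97 and 4.7%. m = 750, ICC 0.05, CAC 0.9 gives DE = 1 + 749 × 0.05 × 0.1 − 0.4 = 4.34 and 34.7%. m = 7,500, ICC 0.05, CAC 0.8 gives DE = 75.6 and 82.2%.

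**Simulation** (20 practices of 750, probit model, ICC on the latent scale, 1,000 runs each). Independent records: 5.0%. 80% overlap only: 2.0%. Stable practice effect only: 5.1%. ICC 0.05 with 80% overlap: 29% at CAC 0.9 and 40% at CAC 0.8. The pattern agrees with the formulas.

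**The case against.** Four points can be made for the plan.

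- **A condensed article leaves model detail to an analysis plan, mentions covariate regression and declares an interrupted time series.** True, but the chi-square and its threshold are stated, not omitted. The regression sentence names no practice or repeated-measures term, and neither it nor the declared design replaces the chi-square as the primary test.
- **The same practices supply both periods, so practice effects cancel.** This stands for stable differences, as the 5.0% and 5.1% results show. It does not hold for differences in change, on which the article gives no figure. The possibility of inflation is established; its size in this trial is not.
- **The test may be conservative.** This also stands for small domains. Management is restricted to patients with CKD and 12 months of follow-up. At 5,000 patients the error stays below 5% until the SD of change reaches about 3 points.
- **The largest figures use a denominator that does not apply.** This stands for two domains. Screening concerns patients at risk and management patients with CKD, so 150,000 is an upper bound that could be approached at most by diagnosis.

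A reader might go further and infer that planned confidence intervals are wrong, or that most patients are known to appear twice. The article supports neither. The section plans no intervals for the primary outcomes, so the point concerns the p-value and its implied standard error. Patient overlap is an inference from the design.

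**Conclusion.** The point holds. The plan fixes a test for the primary outcomes whose independence assumption the design breaks, and p < 0.05 therefore does not carry a 5% type I error. The direction can differ between the three domains: probably inflated where thousands of patients per practice count, possibly deflated where few do.

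The sizes rest wholly on the assumed baseline, correlation, spread of change and denominators, and on reading the null as no average change across practices. Less patient overlap than assumed would weaken the deflation and raise every figure in the table. It would be wrong to conclude that the standard error is always far too small, or to take 77% as the expected error rate. What the documents support is that the error rate is uncontrolled.

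**What to change.** Replace the chi-square as the primary test with a segmented regression that matches the declared interrupted time series, fitted to practice-by-month numerators and denominators for each domain. Take inference with practice as the cluster, in one of two ways:

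- GEE with a bias-corrected robust variance for few clusters and a t reference on about 20 − 1 = 19 degrees of freedom. With practice-level robust variance, repeated patients within a practice are also covered.
- A mixed model with random level and slope change per practice that also allows for residual month-to-month autocorrelation. Aggregation to practice-months alone does not deal with repeated patients here, and a cumulative indicator such as coded diagnosis will be strongly autocorrelated.

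The Kenward-Roger correction belongs to linear mixed models and should not be named for a binomial model or for GEE. Patient-level secondary analyses should account for patients nested in practice. The chi-square can remain as a descriptive summary without a decision rule.

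Cost: analysis wording and programming. The extract must carry a practice identifier. The article does not state this outright, but outcome 1.7 implies it. Intervals will usually be wider for the large-denominator domains.

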## Discussion

This study describes an evaluation of a real-world implementation trial of a clinical decision support and quality improvement software for CKD in the primary care setting, supported by the tertiary health service. This is in contrast to the traditional silos that exist between the primary and tertiary healthcare system in Australia. The trial design enables evaluation of clinical and health service outcomes of the intervention, in addition to an implementation evaluation.

There has been considerable effort to improve chronic disease management in primary care and a systematic review by Neale et al. identified that technology and enhanced collaboration were important enablers in improving CKD care in primary care [6]. There has been mixed success with clinical decision support software (CDSS) more broadly with high heterogeneity between interventions [17, 18]. A qualitative systematic review identified key recommendations for CDSS implementation including enhancing the clinical process, providing relevant clinical information, appropriate education and training, integration into standard workflow, and need for further research and design in multimorbidity [19]. This trial aims to address these recommendations with the co-design process ensuring integration into current primary care workflows, staff education and ongoing support, and use of a practice champion. Additionally, whilst the focus of this protocol is analysis of kidney disease outcomes, included modules in the FHT program address the common co-morbidities of diabetes and cardiovascular disease.

Earlier detection and management of CKD requires time for improvements to be realised, hence a three-year trial duration was chosen. One limitation of a pre-post implementation trial with a historical control is the inability to assess direct causation. This approach was chosen given the practical challenges of a randomised trial in primary care over three years in addition to the ethical challenges of preventing practices from undertaking quality improvement and CKD educational activities over this extended duration. To help address this limitation an interrupted time series design has been chosen with a 3-year retrospective control compared to the 3-year prospective intervention used to assess the rate of change in parameters over time. This will assist in determining if improvements are due to a natural increase in screening, diagnosis, and management over the course of time, or associated with the intervention.

